### Analyses

#### Feasibility

Feasibility will be assessed through several indicators, including recruitment and retention rates, number and reasons for drop-outs, and adherence to the planned sessions. Acceptability and tolerability of the protocol will be evaluated based on participants' feedback, the presence of adverse events or side effects, as measured with the TMSens_Q, and overall satisfaction with the intervention as measures with a likert scale from 0 to 100.

#### Clinical, behavioral and cognitive outcomes

Analyses will be conducted according to the intention-to-treat principle. For each outcome, longitudinal changes will be evaluated using linear mixed-effects models (LMMs) with fixed factors of Group (active vs. sham), Time (baseline, post-treatment, 4-month follow-up), and their interaction (Group × Time). Random intercepts for participants will be included to account for within-subject correlations across repeated measurements. Effect sizes and 95% confidence intervals will be reported alongside p-values.

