#### Clinical evaluation

At all three time points, an independent psychiatrist will conduct a semi-structured interview, systematically addressing expectations and concerns about TMS, anxious and depressive symptoms, daily functioning and quality of life, ruminative and repetitive thoughts, and core eating disorders psychopathology. Additional domains such as obsessive-compulsive symptoms, impulsivity levels, and levels of insight will be explored if clinically relevant. This qualitative assessment will complement standardized scales in evaluating symptom change and treatment acceptability. From this interview, the following outcome measures will be extracted: body weight and BMI, presence or return of menses, and any modification of the psychopharmacological treatment. In addition, the psychiatrist will record changes in eating behaviors (restriction, binge episodes, purging, and excessive compensatory exercise), levels of preoccupation with weight and body image, mood and anxiety severity, and global clinical impression (CGI-S/CGI-I). These measures will provide complementary indicators of treatment response and acceptability alongside standardized scales.

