
## Discussion

The present protocol introduces an attempt to broaden the application of TMS in AN by moving beyond the prefrontal cortex, which has so far represented the predominant neuromodulation target (Bahadori et al., 2025). Here, stimulation is directed to the PPC with the aim of modulating neural systems involved in body representation and in the emergence of rigid, implicitly driven eating behaviors, two domains that are central to the disorder and often resistant to conventional treatments. Target localization is individualized on the basis of resting-state connectivity, identifying posterior parietal nodes with the strongest co-activation within circuits relevant to body representation and cue-triggered eating behaviors. This approach provides a neurobiologically informed rationale for intervention and aligns with the principles of precision psychiatry, by tailoring stimulation to networks relevant in the maintenance of specific symptom dimensions (Williams et al., 2024). The outcome assessment is designed to span multiple levels. Core clinical outcomes include body weight and BMI, menstrual status, and changes in eating disorder psychopathology. Broader psychopathological dimensions such as anxiety and depression are also systematically evaluated. In addition, the study places particular emphasis on implicit processes related to body representation and food-related behavior, domains that are less accessible through self-report measures. To this end, the protocol incorporates experimental paradigms delivered through virtual reality and mobile applications, allowing the capture of distortions in body representation and automatic responses that are rarely addressed in routine clinical assessments. Together, these multimodal measures aim to provide a more comprehensive picture of treatment effects, bridging clinical symptomatology with underlying cognitive processes and neural mechanisms.

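### The linear mixed model set for all clinical outcomes does not suit yes/no menstrual status, and its p-values and intervals can be materially off if menses go from rare at baseline to common at follow-up

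*Protocol article*

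**What the plan says.** Under Analyses, the section on clinical, behavioral and cognitive outcomes states: "For each outcome, longitudinal changes will be evaluated using linear mixed-effects models (LMMs"), with Group, Time (baseline, post-treatment, 4-month follow-up) and their interaction as fixed effects. It adds: "Random intercepts for participants will be included to account for within-subject correlations across repeated measurements". On reporting: "Effect sizes and 95% confidence intervals will be reported alongside p-values". It names no exception by type of outcome and no model for binary, ordinal or count data.

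The Clinical evaluation section says which measures come from the psychiatrist's interview: "the following outcome measures will be extracted: body weight and BMI, presence or return of menses, and any modification of the psychopharmacological treatment". The Discussion then says: "Core clinical outcomes include body weight and BMI, menstrual status, and changes in eating disorder psychopathology".

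Feasibility has its own descriptive section, and connectivity is analysed by a 2 x 2 mixed ANOVA. The linear-model rule therefore covers the clinical, behavioral and cognitive outcomes, not everything in the trial.

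**The concern.** Presence of menses is 0 or 1 at each visit. Its variance is p(1-p): close to zero when almost nobody menstruates and largest near one half. A random-intercept linear model assumes a single residual variance and equal correlation across T0, T1 and T2. If prevalence rises over the trial, the pooled variance is too large for the early contrast and too small for the late one. A real difference at T1 is then harder to see, and a chance difference at T2 is declared more often than the stated 5%. The model can also give intervals that include impossible proportions.

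The abstract says that effect-size data from this trial will guide a confirmatory trial. An interval of the wrong width on an outcome described as core is poor input for that.

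This is not a detail left to a statistical analysis plan. The article states a rule, and the rule does not fit one of the outcomes it covers.

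**Working it through.** **The plan's own figure.** Sample-size inputs from Participants and recruitment: f = 0.25, alpha = 0.05, power 0.80, r = 0.5, 2 groups, 3 times.
- Noncentrality = f² x N x 3 / (1 - r) = 0.0625 x 28 x 3 / 0.5 = 10.5, with df 2 and (28 - 2) x 2 = 52.
- Power is 0.812 at N = 28 and 0.778 at N = 26, so 28 reproduces. 28 x 1.2 = 33.6, rounded up to the planned 34.
- This rests on a continuous outcome and does not depend on how menses are analysed.

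**Why one pooled variance misleads.** Assume rates of 2%, 5% and 30% at T0, T1 and T2 in both arms, from a latent normal variable with correlation 0.8 between visits. The probabilities of menses at both visits of a pair are then 0.0134 (T0, T1), 0.0197 (T0, T2) and 0.0479 (T1, T2). The variance of a within-person change is pj(1 - pj) + pk(1 - pk) - 2(pjk - pj pk):
- T1 - T0: 0.0196 + 0.0475 - 2(0.0134 - 0.0010) = 0.0423
- T2 - T0: 0.0196 + 0.2100 - 2(0.0197 - 0.0060) = 0.2022
- T2 - T1: 0.0475 + 0.2100 - 2(0.0479 - 0.0150) = 0.1917

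The model uses the average for every contrast: (0.0423 + 0.2022 + 0.1917) / 3 = 0.1454.
- The T2-versus-baseline standard error is too small by a factor of √(0.1454 / 0.2022) = 0.85.
- The T1 standard error is too large by a factor of √(0.1454 / 0.0423) = 1.85.
- With critical value 2.007 (52 df), a normal approximation to T2 rejection is 2Φ(-2.007 x 0.848) = 0.089 instead of 0.05.

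**Simulation under no treatment effect.** The balanced random-intercept analysis was reproduced as a split-plot analysis with pooled within-subject error, 14 or 17 per arm, latent correlation 0.5 or 0.8. All rates are assumptions.

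| Rates T0/T1/T2 | Group x Time | T1 contrast | T2 contrast |
|---|---|---|---|
| 2/5/30% | 6.8-7.5% | about 0.1% or less | 8.6-10.1% |
| 10/12/35% | 5.3-5.9% | 0.8-1.6% | 6.6-8.0% |
| 30/35/40% | about 5% | about 4.5% | about 5% |

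Continuous normal data run through the same code give 4.9% rejection and 95.2% coverage, so the departures come from the outcome type. At 17 per arm and latent correlation 0.7, the T2-versus-baseline interval covers 90.9% at 2/5/20%, 90.0% at 0.1/5/30%, 93.3% at 10/20/40% and 95.0% at 30/35/40%. Going from 14 to 17 per arm changes little.

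**An impossible interval.** Suppose 1, 1 and 3 of 17 menstruate at the three visits in one arm, and 1, 2 and 6 of 17 in the other.
- The sum of squares about the six cell means is 3 x (16/17) + 42/17 + 30/17 + 66/17 = 10.94. On 3 x 32 = 96 degrees of freedom the pooled variance is 0.114 (SD 0.338).
- The binomial variance is 0.055 in a baseline cell (about half the pooled value) and 0.228 in the 6/17 cell (about twice it).
- The approximate interval for the baseline proportion is 0.059 ± 2 x 0.338 / √17, that is -0.10 to 0.22.

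**A binary-data comparison.** At T2 with 17 per arm and true rates of 10-40%, Fisher's test rejects in 0.8-2.2% under no effect, and the Newcombe interval covers 94.7-96.9%. Power for 10% versus 40% is about 39%.

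**The case against.** The strongest reply concerns scope and consequence. The quantitative primary outcome is BMI and questionnaire scores, for which a linear mixed model is suitable. No hypothesis and no sample size rests on menses, the word core appears only in a Discussion sentence, and this is a feasibility trial. All of that stands and keeps the point modest. It does not make the stated rule fit a binary outcome.

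It can also be said that an analysis plan would set models by outcome type, and that the sentence was meant for scored scales. The wording is literal, however, and makes no such exception.

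Four stronger readings are tempting and not supported:
- **That the results for every outcome are wrong.** Feasibility and connectivity have their own analyses, and the scored scales suit the model.
- **That the 7-10% is the error of the test the plan names.** It belongs to a T2-versus-baseline contrast, a natural follow-up that the article does not specify. The named Group x Time test rejects in about 5-7.5%.
- **That binge and purge counts are mishandled.** The article says only that "the psychiatrist will record changes in eating behaviors (restriction, binge episodes, purging, and excessive compensatory exercise"). It gives no scale and calls the psychiatrist's measures complementary: "These measures will provide complementary indicators of treatment response and acceptability alongside standardized scales". Reading them as counts is inference. In simulated zero-inflated counts with no effect, the interaction test was conservative (1.9-3.0%) and contrast coverage was 95.2-96.5%.
- **That the menses outcome is undefined for those menstruating at T0.** The measure is "presence or return of menses, and any modification of the psychopharmacological treatment", and presence is defined at every visit. Only the return part needs a restricted group.

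**Conclusion.** The point holds in a limited form. The article prescribes a linear model with one residual variance for a group of outcomes that includes yes/no menstrual status, and that model is unsuitable for it. The resulting p-values and intervals can be materially miscalibrated, but only if prevalence changes markedly: false rejection of about 5-7.5% for the interaction, about 7-10% for the T2-versus-baseline contrast and under 2% at T1, with interval coverage falling to about 90% in the worst case tried. With rates of 30-40% throughout, error is near nominal.

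These figures assume the stated prevalences, equal latent correlation between visits of 0.5-0.8, complete data and 14-17 per arm. The article reports no menstrual rates, so neither the size nor the direction at a given visit can be settled from it. A reader might infer that the error is certain; it is not. The BMI and questionnaire primary outcomes and the sample size of 34 are untouched.

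**What to change.** Limit the linear mixed model to approximately continuous outcomes. For menstrual status, name a method for binary data, for example an exact or Firth-penalised comparison by arm at T1 and at T2 with a confidence interval. Compare return of menses among participants without menses at T0. For other non-continuous measures, such as the CGI ratings and medication change, state the recorded scale and use a model that matches it.

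This changes wording only; no data or participants are added. There are two small costs: the return-of-menses comparison uses fewer participants, and an exact test is conservative at this sample size, so the interval should carry most of the interpretation.

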
The primary outcome of the study will be clinical improvement, assessed quantitatively through changes in BMI and scores on eating disorder psychopathology questionnaires, and qualitatively through the clinical judgment of the psychiatrist. We hypothesize that patients assigned to the active stimulation group will show greater BMI increase and greater reduction in psychopathology compared to the sham group.

Given that the stimulation protocol was specifically designed to target body representation and automatic tendencies toward food, secondary outcomes will focus on these aspects. Changes in body representation will be assessed using both an implicit task, which provides a measure of patients' perceived body boundaries, and an explicit task, in which patients will be asked to select the silhouette that best represents their own body. We hypothesize that, following the stimulation protocol, patients will show a more accurate representation of their body, selecting a silhouette closer to their actual body and demonstrating more precise boundary estimations.

Implicit behavioral tendencies toward food will be assessed using an approach–avoidance task. In a previous study, we observed that patients with AN exhibited a reduced tendency to approach food stimuli (Meregalli et al., 2024). We expect that, following the stimulation protocol, a more natural behavioral tendency will be restored, characterized by faster automatic approach of food stimuli.

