### Participants and recruitment

Participants will be recruited from the Eating Disorder Center of the Hospital of Padova, Italy. All eligible female patients followed at the center will be invited to take part in the study, as an adjunct to TAU, in agreement with their treating clinician. Recruitment will be limited to female patients due to the low number of male patients accessing the center and to minimize potential gender-related confounding factors.

Inclusion criteria will be: (1) current diagnosis of AN according to DSM-5 criteria; (2) age ≥18 years; (3) unsuccessful completion of at least one 3-month course of outpatient treatment; (4) illness duration of at least 1 year, and (5) female gender.

Exclusion criteria will be: (1) Presence of significant neurological comorbidities or severe/unstable systemic diseases, (2) Diastolic blood pressure < 60 mmHg or heart rate < 60 bpm, (3) diagnosis of psychosis or substance abuse disorders, (4) history of hypomanic/manic episodes, (5) Current suicidal ideation, (6) known contraindications to TMS as assessed with the TMS safety checklist (Rossi et al., 2021), including epilepsy, head trauma with loss of consciousness, severe/frequent headaches, cochlear implants, pacemakers, pregnancy, metallic implants, implanted neurostimulators; and (7) known contraindications to MRI, as assessed with the Hospital of Padova MRI safety checklist (Mod. Rev. 2, 16/05/2023), including presence of medical devices or metallic material, history of surgery or significant physical trauma, claustrophobia, pregnancy.

*A priori* power analysis conducted with G^*^Power (Faul et al., 2007) indicated that 28 participants are required to detect a significant group (2) × time (3) interaction assuming a medium effect size (Cohen's *f* = 0.25), statistical power of 1–β = 0.80, and significance level α = 0.05, with a correlation among repeated measures of *r* = 0.5. To account for potential dropouts, the sample size will be increased by 20%, resulting in a final target enrollment of 34 participants.

The study has been approved by the Ethics Committee of the Hospital of Padova (protocol number 6168/EST/25) and registered on ClinicalTrials.gov (registration number: NCT07106645). Written informed consent will be obtained from all participants prior to enrollment. Participants will be informed that their involvement is voluntary and that they may withdraw at any time without any consequences for their ongoing treatment.

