### Intervention

#### Treatment as usual

In this study, iTBS is delivered as an add-on to treatment as usual (TAU) provided by a specialized eating-disorder service. TAU reflects a guideline-consistent, multidisciplinary and coordinated care pathway, and may include: (1) nutritional rehabilitation with dietetic assessment and monitoring, (2) regular medical monitoring of physical status and risk parameters, (3) eating-disorder-focused psychological support/psychotherapy, (4) psychoeducation, and (5) when indicated, family involvement/support. Pharmacological treatment may be part of TAU when clinically indicated. To reduce TAU-related confounding, the type and intensity of TAU will be kept as stable as clinically feasible during the 4-week stimulation period; any changes in treatment setting/intensity or medication will be prospectively documented. TAU intensity variables (e.g., outpatient vs. day-hospital setting, frequency of clinical/psychological/dietetic contacts, and medication changes) will be monitored throughout the study and considered in sensitivity analyses (and as covariates where appropriate).

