#### Functional connectivity modifications

In order to assess if behavioral modifications will be accompanied by an underlying change in the connectivity of the TMS target, we will statistically compare pre and post connectivity estimates by means of a 2 × 2 mixed Analyses of Variance (ANOVA), with the two factors representing respectively the Group (active vs. sham, between-subjects) and the Time (baseline vs. post-treatment, within-subject). The graph theory framework will be used to verify our hypothesis that the individualized stimulation protocol will result in enhanced connectivity between the parietal TMS target and the networks' overlap map (i.e., the conjunction between the neural regions involved in body schema representation and in implicit behavioral tendencies). In more detail, we expect the active group to show increased connectivity, i.e., a lower path length, in the post-treatment compared to the pre-treatment scan between these two sites, where the path length is measured as the inverse of the connectivity strength. At the same time, we expect that the broader network of regions involved in both body schema and implicit behaviors will show greater global efficiency, which reflects enhanced integration between distant nodes and is mathematically computed as the inverse of the averaged path lengths between all pairs of nodes, such as that short paths between all pairs of nodes translate in greater global efficiency of the overall network. We expect increased global efficiency as a result of the repeated activation of the targeted regions by means of the stimulation. Finally, in consideration of the fact that the TMS-induced effects on the functional connectivity can extend beyond the stimulation target (Beynel et al., 2020), we will address potential changes in the overall connectivity of the brain. In particular, we will test if the brain connectome might benefit from a functional re-arrangement that might lead to a concomitant increase in both global (every region can be linked by means of a short few paths) and local (regions cluster together into specialized modules) efficiency. This property is known as small worldness, which the literature suggests being decreased in AN patients compared to controls (Geisler et al., 2020). Small-worldness reflects hence the ratio between the average path length of a network and its clustering coefficient (i.e., a measure of the tendency of neighboring nodes to form triangular triples and thus to display high local efficiency).

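### The efficacy model uses baseline as an outcome level, not as an adjustment: the test is valid, but precision is lost at the plan's own r = 0.5

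*Protocol article*

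**What the plan says.** Under Analyses, Clinical, behavioral and cognitive outcomes, the article fixes one model for each outcome: "fixed factors of Group (active vs. sham), Time (baseline, post-treatment, 4-month follow-up), and their interaction". On the covariance it adds: "Random intercepts for participants will be included to account for within-subject correlations across repeated measurements".

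The sample size under Participants and recruitment is computed for the same test: "28 participants are required to detect a significant group (2) × time (3) interaction assuming a medium effect size". Its inputs are f = 0.25, power 0.80, α = 0.05 and r = 0.5. Adding 20% for dropout gives 34.

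The hypothesis in the Introduction is that "patients assigned to the active stimulation group will show greater BMI increase and greater reduction in psychopathology compared to the sham group".

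For connectivity, Functional connectivity modifications plans a "2 × 2 mixed Analyses of Variance (ANOVA") with Group and Time (baseline, post-treatment).

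The only covariates named are treatment-as-usual intensity variables (Treatment as usual). The baseline outcome value is not named as a covariate, and the arms are not constrained to a common baseline mean. The Figure 2 caption places randomization after the baseline assessment.

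**The concern.** Baseline is measured before randomization, so the two arms have equal baseline means in expectation. The stated model still estimates a separate baseline mean for each arm and subtracts it in full. When the correlation between visits is below 1 and the SDs are equal, full subtraction carries more baseline noise into the contrast than regression on the baseline value does.

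What is at stake is the width of the intervals, the power for the efficacy hypotheses, and the stability of the effect sizes that are meant to guide a confirmatory trial (Abstract, Discussion). With 17 per arm, the baseline difference between arms has a standard error of √(2/17) = 0.34 SD. At r = 0.5, a chance imbalance of that size moves the raw-change contrast by (1 − 0.5) × 0.34 = 0.17 SD in the trial at hand.

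**Working it through.** **Inputs.** From Participants and recruitment: f = 0.25, r = 0.5, α = 0.05, N = 28 (target 34). Allocation is 1:1 (Abstract). Assumptions not in the article: equal SDs at T0, T1 and T2 (set to 1), and the pattern of the effect over visits.

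**1. The plan's figure.** λ = f²·N·3/(1 − r) = 0.0625 × 28 × 3/0.5 = 10.5, with df 2 and 2 × (28 − 2) = 52. Power is 0.812. At N = 27 it is 0.795, so 28 reproduces. At N = 34, λ = 12.75 and power is 0.888.

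**2. What the model estimates.** With complete data, the Group × T1 coefficient equals the between-arm difference in mean change. Over 150 simulated trials the largest discrepancy was 2 × 10⁻¹⁵.

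**3. Variance per patient for the T1 contrast.**
- Raw change: 2(1 − r) = 1.00
- Baseline-adjusted: 1 − r² = 0.75
- Ratio: (1 + r)/2 = 0.75, a cut of (1 − r)/2 = 25%

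**4. The 2-df test.** The covariance of (T1, T2) is [[1, 0.5], [0.5, 1]] for change and [[0.75, 0.25], [0.25, 0.75]] after adjustment. With effect vector d, λ is proportional to d′V⁻¹d. For a sustained effect d = (1, 1) this is 1.333 against 2.000, a ratio of 1.50. The ratio is 1.375 if the effect halves by T2 and 1.125 if it is present at T1 only.

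| Effect pattern | λ, N = 28 | Power, N = 28 (planned 0.812) | Power, N = 34 (planned 0.888) |
|---|---|---|---|
| Sustained | 10.5 × 1.50 = 15.75 | 0.942 | 0.976 |
| Halved at T2 | 10.5 × 1.375 = 14.44 | 0.921 | 0.964 |
| T1 only | 10.5 × 1.125 = 11.81 | 0.857 | 0.922 |

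**5. The T1 contrast alone.** For a sustained or T1-only effect, f = 0.25 corresponds to a difference of 0.25 × √18 = 1.06 SD. A t-test on change has power 0.771 and the adjusted analysis 0.876 (N = 28). At N = 34 the figures are 0.851 and 0.933.

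**6. Sensitivity to r.** The effect is rescaled so that the planned test keeps power 0.81 at N = 28.

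| r | T1 variance cut | Adjusted power, sustained | Adjusted power, T1 only |
|---|---|---|---|
| 0.3 | 35% | 0.98 | 0.89 |
| 0.5 | 25% | 0.94 | 0.86 |
| 0.7 | 15% | 0.89 | 0.84 |
| 0.9 | 5% | 0.84 | 0.82 |

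**7. If the covariance must be estimated.** With 4,000 simulated trials (N = 28, r = 0.5), the planned test was compared with a baseline-adjusted test using an unstructured covariance. Power went from 0.826 to 0.918 (sustained), 0.809 to 0.890 (halved) and 0.799 to 0.816 (T1 only). Type I error was 0.045 and 0.050.

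**8. If SDs differ between visits.** Let k be the ratio of post-baseline to baseline SD (an assumption; the article gives no SDs). Suppose the Group term is dropped but the random intercept is kept. The implied baseline slope b is then the pooled covariance over the pooled variance, and the T1 variance is k² + b² − 2b·rk, against k² + 1 − 2rk as planned. For k = 1.5 and r = 0.7:
- b = 1.225/1.833 = 0.668
- variance 2.25 + 0.446 − 1.403 = 1.293 against 1.150, a ratio of 1.12

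At k = 1.25 and r = 0.7 the ratio is 1.02; at k = 1.5 and r = 0.5 it is 1.01. ANCOVA has variance k²(1 − r²), which never exceeds the planned one in large samples. Its ratios are 0.98 (k = 1.25, r = 0.7) and 1.00 (k = 1.5, r = 0.7).

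**The case against.** The strongest reply is that nothing here is an error. The Group × Time model is valid under randomization, it is the test that the sample size was computed for, and it delivers the stated power. No section contradicts another, the trial is described as a feasibility trial, and further covariates may be set out in an analysis plan that is not shown. All of this stands, except that the article does not leave the model open: it names the fixed and random effects, and that specification is the less precise one at its own planning correlation.

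A reader might infer that the planned estimate is biased, because an arm that starts worse by chance tends to improve more. The documents do not support this. Over repeated randomizations the estimator is unbiased; chance imbalance is a matter of precision.

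A reader might also infer that every Group × Time contrast is affected. The T2-versus-T1 contrast does not involve baseline, and with missing visits the likelihood estimate is no longer exactly a difference in raw mean change.

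Finally, a reader might infer that any form of baseline adjustment can only help. Step 8 shows otherwise: a common baseline mean combined with the stated random intercept can be less precise than the planned model when SDs differ. Spread that grows after entry is plausible for BMI, since patients are selected on a current diagnosis. At r = 0.5, even ANCOVA then cuts the T1 variance by only 11% (k = 1.25) or 4% (k = 1.5).

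**Conclusion.** The point holds as a loss of precision, not of validity. At the plan's f = 0.25, r = 0.5 and N = 28, with equal SDs, baseline adjustment raises the power of the 2-df test from 0.81 to between 0.86 and 0.94, depending on how the effect develops over visits. It cuts the T1 contrast variance by a quarter, which is worth a third more patients (1/0.75 = 1.33).

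The gain is not uniform. It shrinks to a 5% variance cut at r = 0.9, which may apply to BMI (an assumption; no outcome-specific correlation is given). It is only about 2 power points for a T1-only effect when an unstructured covariance has to be estimated. For connectivity the form of the test is the same, but the size of the gain is unknown because no connectivity correlation is stated. The change is worth making because the baseline values are already collected.

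**What to change.** In Clinical, behavioral and cognitive outcomes, choose one of two forms:

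- Model T1 and T2 as outcomes, with Group, Visit, Group × Visit, the baseline value and baseline × Visit.
- Keep T0, T1 and T2 as outcomes with a common baseline mean (Time, Group × T1, Group × T2, no group difference at T0), and replace the random intercept by an unstructured covariance over the three visits. This form keeps every randomized patient who has a baseline, in line with the stated intention-to-treat principle. It should not be combined with the random intercept alone.

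Report the T1 and T2 contrasts with their intervals. In Functional connectivity modifications, test the group effect by ANCOVA of the post-treatment value on Group and the baseline value.

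Leave the sample size unchanged. The cost is wording, plus about one degree of freedom per adjusted outcome for ANCOVA or a few extra covariance parameters for the common-baseline model. No new data are needed.
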